
### Immersive Virtual Reality training

#### Virtual scenarios.

The virtual scenarios and objects were developed in Blender 3D (https://www.blender.org/) and implemented in Unity Game Engine (https:/www.unity.com/). The scenarios were designed to represent realistic settings and situations appropriate for the age groups of participants (adolescents and adults). In detail, the scenarios for adolescents presented a school library and an outdoor playground, while the scenarios for the adults included a supermarket and a restaurant.

In addition, a practice scenario was created for each age group, to be presented at the beginning of the first training session only. The layout, objects and trial structure of this scenario are identical to those in the experimental scenarios, but the scene does not contain any details to identify the virtual space; the virtual objects are simple 3D geometric figures, and the avatars are represented as grey shapes without distinct features. All scenarios have a similar layout that included a surface (a counter) where the virtual objects were placed, which is located in front of the participant, and a door at the far frontal end of the room/space (Fig 4A).

**Fig 3 pone.0353955.g003:**
[figure not shown]
HD-tACS electrodes montage and E-field Simulation. Representation of the estimated electric field induced by cerebellar IGF HD-tACS using five 3,14 cm^2^ round electrodes, the active electrode placed over the left posterior cerebellum (centered 2 cm below and 3 cm to the left of the inion) while the four reference electrodes will be positioned in a circle and equidistant from the center (4 cm). The head model was created using fine element modeling on T1- and T2-wighted MRI images of an exemplary subject resulting in a high-resolution tetrahedral head mesh model containing 8 tissue types. Electrodes of 1 mm thickness were simulated with 2 mm thick of conductive gel. All tissues were treated as isotropic. The electrical field E was determined by taking the numerical gradient of the electric potential.

Four virtual avatars were created for each set of scenarios (adolescent and adult versions) with MakeHuman (http://www.makehumancommunity.org/) and iClone 3D (www.reallusion.com) software. The avatars’ body size and features were age-matched with age of the two target groups (i.e., adolescents and adults). In both sets, two avatars were male and two were female, and all avatars differed in certain characteristics such as hair color, hairstyle, and clothing (Fig 4B). All avatars were animated in Unity Game Engine with the animation of naturalistic walking. The scenarios will be presented to the participants via a Meta Quest 2 head-mounted display (HMD) with RGB LCDs with 1832x1920 pixels resolution, refresh rate at 120 Hz, the field of view of 110° (diagonal FOV) and 6 degrees of freedom. Participants will interact with the content of the scenarios via Meta Quest 2 hand-held game controllers for both hands.

**Fig 4 pone.0353955.g004:**
[figure not shown]
Immersive Virtual Reality (IVR). A) Virtual scenarios for adult patients (top left panel: supermarket scenario, top right panel: restaurant scenario) and adolescent patients (bottom left panel: library scenario, bottom right panel: playground scenario); B) Virtual avatars for the adults’ (left panel) and adolescents’ (right panel) scenarios. This figure was created by the authors and also featured in Siciliano et al., [68].

### Procedure

In all the scenarios, participants observe the virtual scene from the first-person perspective. The only visible part of their virtual body is the hands, which move synchronously with participants’ hand movements performed with the game controllers. In the scene, participants are located above a chair in front of the counter that is reachable with a forward hand movement. At the onset of each trial (activated by the participants via pressing the A key on the right controller), three different objects appear on the counter in front of the participant. Together with the appearance of the objects, one of four avatars enters the scene through the door located in the far front end of the scene. The avatar approaches the counter by walking at a constant speed and grasps one of the objects. In the first four trials, participants are instructed to observe the avatars and the objects without performing any movements. After that, participants are asked to anticipate which object the avatar would grasp and to grasp that object themselves before the avatar does. Once either the avatar or the participant grasps one of the objects, the avatar and the objects disappear and the trial is concluded.

The virtual objects in each scenario belongs to one of three categories: in the supermarket, the categories include packaged foods, beverages and household products; in the restaurant, the objects belong to the categories of foods, beverages and sauces; in the library, the objects are books, pencil cases and stationery objects; in the playground, the objects are stuffed toys, books and flowers; in the practice scenario, the objects are cubes, cylinders and spheres with sizes matching those of the objects used in the other scenarios. In each scenario, three avatars show a preferred category of objects that they grasp in all trials, while the fourth avatar picks the objects randomly from any category. The avatar-object category mapping are pseudorandomized and differ across the eight training sessions; moreover, in addition to the object preferences, avatars’ clothes change between the scenarios, in order to prompt the participant to focus on the participant’s identity, rather than simply associating each object with cloth colour. Each of the experimental scenarios include 44 trials that last approximately 7 minutes in total. Within each training session, the two scenarios developed for the age-group are presented in two different blocks, the order of which is counterbalanced across participants. Thus, each training session lasts for approximately 30 minutes.

Before starting the experimental scenarios, participants sit on a chair in a lab with enough surrounding area to safely perform the reaching movements. They are instructed to sit with their back against the back of the chair and their arms placed on the armrests, after which they put on the HMD and take the controllers in each hand. Then, only at the beginning of the first training session, the practice scenario is launched, and the participants could first take a few moments to gain confidence with the virtual environment, performing hand movements, looking around, and describing what they see. These actions are also performed in the beginning of each training session and are necessary to create a sense of embodiment and presence in the virtual environment [69]. In the practice scenario, the structure and the aim of the task are explained, that is participants are instructed how to grasp the virtual objects, how to start the trials, and what the main goal of the task is (predicting the avatars’ preferences in picking the objects and grasping that object before the avatar). Crucially, participants are informed that all avatars may show a preference for one category of objects. If the participants grasps the correct object (i.e., the target object of the avatar), a high-pitched sound is delivered via the HMD speakers; otherwise, a low-pitched sound marks erroneous responses. Participants then perform several trials of the practice scenario until they are comfortable with the grasping movement and the procedure. After that, they perform the two experimental scenarios that will be presented in a counterbalanced order.

### Sample size calculation

Using the GPower 3 software [70] with the “as in SPSS option”, we estimated that, with a mixed design between (group factor: active group vs. sham group) – within (Time points: T0, T1, T2, numerator DF = 2), a sample of 15 subjects per group allows detecting moderate to large effects (f (U)=0.428), based on previous study of the effects of cerebellar electrical stimulation on action prediction tasks in patients with cerebellar malformation [32] with a power of 0.80, setting a significance threshold of 0.05. Hence, 30 CM patients and 30 CA patients will be recruited.

### Statistical analyses

Data analysis will be conducted using Jamovi 2.6. Demographic and clinical variables of the two groups of patients will be inspected through descriptive statistics. Independent sample t test (two-tailed) and χ2 will be used to assess the differences between the experimental and control training groups at baseline for continuous and categorical variables, respectively, thus allowing us to verify successful randomization.

Normality of data distribution will be assessed using the Shapiro-Wilk test, whereas the Levene’s test will be used to assess the homogeneity of the variances. Parametric statistical tests will be used if data will result normally distributed, with proper corrections if the assumption of variance homogeneity was violated.

To evaluate intervention efficacy, an intention-to-treat analysis approach will be adopted, including in the analyses all the participants who are allocated into the two study groups and complete at least one evaluation, irrespective of adherence to treatment (i.e., if they do not complete all the training sessions) and evaluations (i.e., if they do not complete evaluations at all time points). No imputation of missing data will be used considering the limited sample size and observation points.

Linear mixed models (LMMs) will be used to treat data considering each primary outcome measure as a dependent variable in separate models. Treatment (active vs. sham HD-tACS as between-subjects variable), time (T0, T1, and T2) and their interactions will be entered as fixed factors, while patients included will be entered as random factors. To take into account a-priori sample differences (even if not statistically significant), we will also consider the age and IQ of participants as possible covariates in follow-up analyses. If one of these covariates will result statistically significant, data will be stratified according to homogeneous values of the significant variable and a secondary analysis will be conducted on homogeneous subgroups for clarifying the effect of the covariates, correcting the alpha level to avoid the possible inflation of first type error. A significance threshold of *p* = 0.05 will be set for all analyses. Post-hoc comparisons will be performed only on statistically significant factors to identify the significant difference between the levels of the independent variables, applying multiple correction methods for type I error. In case of not normally distributed data, the first approach will be the adoption of techniques to normalize data such as the use of z-scores or percentage points; if these kinds of normalization fail, data will be summarized and analyzed by using non-parametric statistics. Data will be reported in terms of median values and quartiles. Instead of LMMs, Kruskal-Wallis analysis for between-subject comparisons will be adopted, together with Friedman’s analysis to compare within-subject parameters. All the analyses will be performed at the end of all T1 evaluations, and no interim analyses will be performed.

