## Abstract

The cerebellum is increasingly recognized for its crucial role in high-level cognitive processes, particularly in the domain of social cognition and action prediction. Disruptions in cerebellar circuits can lead to significant impairments in anticipating others’ intentions and behaviors, affecting daily social interactions. This randomized, double-blind, sham-controlled trial protocol investigates the combined effects of personalized cerebellar High-Definition transcranial Alternating Current Stimulation (HD-tACS) and Immersive Virtual Reality (IVR) training on social prediction abilities. The study involves two clinical populations: adolescents and young adults with congenital cerebellar malformations (CM) and adults with acquired neurodegenerative cerebellar atrophy (CA). Participants undergo eight daily sessions of IVR training designed to enhance internal models of social events through interactive scenarios. Simultaneously, they receive either active or sham HD-tACS delivered at their Individual Gamma Frequency (IGF), determined via baseline EEG. The primary outcomes include behavioral responses to context-based social prediction tasks (action intentions, emotions, and personality traits). Secondary outcomes encompass electrophysiological measures, neuropsychological functioning, and adaptive behavior. By integrating neuromodulation with embodied virtual experiences, the project aims to facilitate cerebello-cerebral plasticity and provide a novel transdiagnostic rehabilitative approach for socio-cognitive impairments. The present protocol has been registered on ClinicalTrials.gov (NCT07500103).

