### Outcomes

#### Primary outcome.

The primary outcomes comprise the behavioural responses to three computer-assisted, context-based social prediction tasks and a non-social control task. These tasks are designed to assess the ability to use contextual information to infer and predict others’ mental states or traits, including action intentions, emotional states, and personality traits. All tasks share the same procedure: each trial presents a priming stimulus (a situational context) followed by an ambiguous target stimulus. In half of the trials, context and target are congruent, confirming the prediction; in the other half they are incongruent, contradicting it. Participants then select between two possible interpretations of the mental state or trait conveyed by the target. In previous studies using similar tasks [45], we found that the preceding situational context influenced participants’ ability to interpret the target: accuracy was higher and reaction times were shorter in congruent than in incongruent trials, indicating that participants used contextual information to infer mental states.

- Action intention prediction task: Contexts are photographs of dining tables (e.g., with empty or filled glasses), followed by an image of a hand reaching toward an object (e.g., a bottle). Pictures are taken before hand–object contact, capturing the pre-shaping of the hand during the reach-to-grasp phase. Participants infer whether the action intends to use the object (e.g., pouring) or to move it (e.g., putting it away).- Emotion prediction task: Contexts are positive or negative social scenarios (e.g., a party, a car accident), followed by morphed facial expressions representing happiness or fear. Participants indicate which emotion is expressed.- Personality trait prediction task: Contexts depict morally acceptable (e.g., helping an elderly person) or unacceptable behaviors (e.g., stealing, polluting), followed by a target face from a validated database [46] normatively rated as trustworthy or untrustworthy. Participants judge whether the face represents a trustworthy person.- Non-social control task: Contexts are indoor or outdoor environments, followed by blurred images of natural (e.g., a tree) or artificial objects (e.g., a ball) from an existing database [47]. Participants classify the target as natural or man-made.

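### Four tasks, one a non-social control, are all primary and each is tested at 0.05 with no error control across them: about 12–19% chance of a false positive per population if any one counts as success

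*Protocol article*

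**What the plan says.** **Primary set.** The Primary outcome section states: "The primary outcomes comprise the behavioural responses to three computer-assisted, context-based social prediction tasks and a non-social control task". That is four tasks: action intention, emotion, personality trait, and natural versus man-made objects as the control. The Abstract names only the social ones: "The primary outcomes include behavioral responses to context-based social prediction tasks (action intentions, emotions, and personality traits".

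**Measure per task.** For this trial the section speaks only of behavioural responses. Accuracy and reaction time appear where it reports earlier studies with similar tasks: "accuracy was higher and reaction times were shorter in congruent than in incongruent trials".

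**Analysis.** The Statistical analyses section says: "Linear mixed models (LMMs) will be used to treat data considering each primary outcome measure as a dependent variable in separate models". Each model has treatment, time (T0, T1, T2) and their interaction as fixed factors. The threshold is general: "A significance threshold of *p* = 0.05 will be set for all analyses".

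**Correction for multiplicity.** That section mentions it twice. Post-hoc comparisons after a significant factor are made "applying multiple correction methods for type I error", and alpha is adjusted for subgroup analyses that follow a significant covariate. Neither provision acts across the primary outcomes.

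**Sample size.** The Sample size calculation section uses one group-by-time design with f(U) = 0.428, 15 per group, power 0.80 and alpha 0.05. The effect size comes from a study of "effects of cerebellar electrical stimulation on action prediction tasks in patients with cerebellar malformation".

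**The concern.** Each population is run as its own randomized comparison with several primary tests, each at the full 0.05. Nothing says how many must succeed, or which, for the treatment to be called effective. After the data are in, whichever task reached 0.05 could be presented as the primary success, and the error rate of that claim would exceed 5%.

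The control task adds to this. Its purpose is to show that any benefit is specific to social prediction, yet it sits in the same primary list and adds another chance of a significant primary result.

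The sample size is also affected. It provides 0.80 power for one test at 0.05, so if a correction were added later with 30 patients per population, the stated power would no longer hold.

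**Working it through.** **1. Reproduce the stated power.** Inputs from the Sample size calculation section: f(U) = 0.428, N = 30 per population, k = 2 groups, m = 3 time points, alpha 0.05, with the SPSS-style effect size option.

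- Noncentrality: λ = f(U)² × (N − k) × (m − 1) = 0.428² × 28 × 2 = 10.26
- Degrees of freedom: 2 and 56
- Power from the noncentral F: 0.804 at N = 30 and 0.770 at N = 28

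The plan's figure is reproduced, and 30 is the smallest even N that reaches 0.80. It applies to one treatment-by-time test at 0.05.

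**2. Chance of at least one false positive in one population.** For n independent tests it is 1 − 0.95ⁿ:

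- Three tests: 1 − 0.95³ = 14.3%
- Four tests: 1 − 0.95⁴ = 18.5%
- Eight tests: 1 − 0.95⁸ = 33.7%

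Whatever the correlation, four tests at 0.05 cannot exceed 4 × 0.05 = 20%.

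The tasks are done by the same patients, so the results will be correlated. The protocol gives no correlation, so 0 to 0.8 is assumed. The interaction F-test was simulated with no treatment effect, 15 per arm, three time points, sphericity, complete data and equal correlation between outcomes. Each simulated cell shows 40,000 runs, then a repeat with 200,000.

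| Tests per population | Independent (exact) | Correlation 0.5 | Correlation 0.8 |
|---|---|---|---|
| 3 (social tasks, one measure each) | 14.3% | 12.8% / 12.9% | 10.1% / 10.2% |
| 4 (all tasks, one measure each) | 18.5% | 15.7% / 16.0% | 11.8% / 11.9% |
| 8 (all tasks, two measures each) | 33.7% | 25.8% / 25.9% | 16.4% / 16.6% |

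The eight-test row is conditional on both accuracy and reaction time being tested for every task.

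**3. Power if alpha is split at N = 30.** Same λ = 10.26 and same degrees of freedom, with alpha replaced:

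| Split | Alpha per test | Power at N = 30 | N per population for 0.80 |
|---|---|---|---|
| None | 0.05 | 0.80 | 30 |
| Bonferroni over 3 | 0.0167 | 0.65 | about 40 |
| Bonferroni over 4 | 0.0125 | 0.61 | about 42 |
| Bonferroni over 8 | 0.00625 | 0.51 | about 46 |

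**The case against.** **No at-least-one rule is written.** If every primary task had to succeed, there would be no inflation. That stands as a condition on the percentages. But the protocol does not state an all-must-succeed rule either, and such a rule would lower the power below the single-test 0.80.

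**Detail may sit in a fuller analysis plan.** This would answer a silent article, but this one is not silent. It sets separate models and one threshold for everything, and says where correction applies. A plan that corrected across the primaries would depart from it.

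**Stronger readings that the protocol does not support:**

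- *A 34% error rate.* A reader might infer this from the mention of accuracy and reaction time. Those measures are named for previous studies only, and 34% also needs eight independent tests.
- *No multiplicity correction at all.* Two corrections are stated. What is missing is one across the primary outcomes.
- *A gain on the control task alone makes the trial positive.* The list permits it formally, but the hypotheses in the Introduction and Discussion concern social prediction, so such a result would not support them. That is why the three-task figure is given as well.
- *The Abstract contradicts the Methods.* The Abstract says that the primary outcomes include the social tasks, which need not be a complete list. The two places should be aligned, but this is not a strict contradiction.
- *Pooling both populations.* Sixteen tests would give 1 − 0.95¹⁶ = 56%, but the two populations are separately sized and randomized, so the error rate is properly judged within each.

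**Conclusion.** The point holds. As written, the plan leaves type I error uncontrolled across the primary outcomes in each population. This is a rule fixed badly, not a detail left out, and it bears on the confirmatory claim itself.

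If any one primary success counts, the false positive chance is about 12–19% for the four listed tasks and about 10–14% for the three social tasks, with one measure each. It reaches about 17–34% only if two measures are tested on all four tasks. The ranges rest on assumed correlations of 0.8 down to 0 and on no treatment effect on any outcome. Even the lowest figure is twice the nominal 5%.

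The stated 0.80 power is correct for one test and does not survive an alpha split at the planned size.

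**What to change.** In each population, treated as its own trial at 0.05:

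1. Name one primary measure for each task and make any other measure secondary.
2. Name the treatment-by-time interaction as the primary test, since that is the design the sample size covers. A treatment main effect in the same model averages over baseline and is not the powered test.
3. Control the familywise error over the three social tasks. One option is a fixed sequence starting with action intention, then emotion, then personality trait, stopping at the first non-significant interaction. The first test keeps alpha 0.05 and the stated power. The effect size comes from cerebellar malformation only, so the atrophy population needs its own reason for this order. Another option is Holm with the power restated: for a single task with the planned effect it is at least the Bonferroni value of 0.65.
4. Take the non-social task out of the primary family and report it as a specificity contrast (social minus non-social treatment effect). Align the Abstract with this list.

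**Cost.** Under a fixed sequence, later tasks are confirmatory only if the earlier ones succeed. No extra patients are needed for the first test. Changing the primary set is likely to be an important modification, which the Ethics and dissemination section requires to be reported to the Ministry and approved by the Ethics Committees. Recruitment is expected to run to December 2026 and the data analysts are blinded, so this can still be done. It should be in place before unblinding and before the analysis planned after the last T1 assessment.

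### The fallback for non-normal data replaces the mixed model with Kruskal-Wallis and Friedman tests, neither of which, as written, tests whether change differs between active and sham

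*Protocol article*

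**What the plan says.** **Efficacy model (Statistical analyses).** Each primary outcome gets its own LMM with patients as random factor: "Treatment (active vs. sham HD-tACS as between-subjects variable), time (T0, T1, and T2) and their interactions will be entered as fixed factors".

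**Sample size (Sample size calculation).** The calculation is for a between-within design, active versus sham by "within (Time points: T0, T1, T2, numerator DF = 2), a sample of 15 subjects per group", which "allows detecting moderate to large effects (f (U)=0.428") "with a power of 0.80, setting a significance threshold of 0.05". From this: "Hence, 30 CM patients and 30 CA patients will be recruited".

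**Hypothesis (Discussion).** Active stimulation is expected to enlarge the gain produced by the virtual reality training. Both arms receive that training.

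**Non-normal data (Statistical analyses).** Shapiro-Wilk is applied to the distribution of the data. If it fails, "the first approach will be the adoption of techniques to normalize data such as the use of z-scores or percentage points". If that also fails, "Instead of LMMs, Kruskal-Wallis analysis for between-subject comparisons will be adopted, together with" Friedman's analysis for within-subject comparisons.

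**Analysis set (Statistical analyses).** The approach is intention-to-treat, "including in the analyses all the participants who are allocated into the two study groups and complete at least one evaluation", whether or not every time point was attended. Missing data are not imputed.

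**The concern.** Because both arms are trained, the question is whether active patients change more than sham patients. Kruskal-Wallis has no time factor and Friedman has no treatment factor. An outcome sent down the fallback branch therefore loses the planned test. Since each primary outcome is modelled separately, the data could decide which outcomes are tested for the interaction and which are not.

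Two ways to a treatment claim would remain. One is a comparison of arms at follow-up which, on raw scores, ignores the baseline. The other is the informal reading that active changed and sham did not, which is not a comparison of arms. The step meant to prevent this, normalising the data, appears unable to do so with the techniques it names.

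**Working it through.** **1. The plan's own figure.** Inputs from Sample size calculation: N = 30 per population, k = 2 arms, m = 3 times, f(U) = 0.428, alpha 0.05. With G*Power's SPSS option:
- df1 = (k − 1)(m − 1) = 2
- df2 = (N − k)(m − 1) = 28 × 2 = 56
- λ = f² × df2 = 0.1832 × 56 = 10.26
- noncentral F power = 0.804, matching the stated 0.80.

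A between-subject test with 1 and 28 df would give 0.590. The trial was therefore sized on the treatment-by-time interaction.

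**2. The normalising step.** Shapiro-Wilk is W = (Σ aᵢx₍ᵢ₎)² / Σ(xᵢ − x̄)², with Σaᵢ = 0. Replacing x by (x − c)/s removes c and divides numerator and denominator by s², so W and its p-value do not move. Numerically, z-scoring 2,000 samples changed W by at most 1.7 × 10⁻¹⁵. A simulated skewed reaction-time sample had W = 0.749 and p = 8.8 × 10⁻⁶ as raw values, as z-scores and as percentages.

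**3. Power in the fallback branch.** Assumptions, none given in the article: normal data with total SD 1, equal correlation ρ between visits, and the same extra gain d at T1 and T2 in the active arm. With 15 per arm, λ = 15 × 2 × ¼ × ⅔ × d²/(1 − ρ) = 5d²/(1 − ρ). Setting λ = 10.26 gives d = 1.432 × √(1 − ρ). Simulation used 4,000 trials per row:

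| ρ | d (SD) | Interaction F | Kruskal-Wallis, raw T1 | Kruskal-Wallis, average of three visits | Rank test, T1 − T0 | Rank test, mean(T1, T2) − T0 |
|---|---|---|---|---|---|---|
| 0.5 | 1.013 | 0.80 | 0.74 | 0.58 | 0.74 | 0.85 |
| 0.7 | 0.785 | 0.80 | 0.53 | 0.32 | 0.74 | 0.85 |
| 0.8 | 0.641 | 0.79 | 0.39 | 0.23 | 0.74 | 0.84 |

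The pattern follows from the variances. A raw T1 score has variance 1, so its standardised effect is d and falls as ρ rises. T1 − T0 has variance 2(1 − ρ), so its standardised effect is 1.432/√2 = 1.013 at every ρ. The mean change has variance 1.5(1 − ρ), giving 1.432/√1.5 = 1.17. At ρ = 0.5 raw T1 and T1 − T0 are equally powerful; the baseline pays off above that.

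With no stimulation effect, rejection rates were 0.046 to 0.050 for Kruskal-Wallis at T1 and 0.048 to 0.055 for the change-score rank tests.

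**4. Friedman, if run by arm.** With no stimulation effect and a common training gain of 0.6 SD, active was significant and sham was not in 25%, 20% and 11% of trials at ρ = 0.5, 0.7 and 0.8. A separate run with gains of 0.3 to 0.7 SD at ρ = 0.5 and 0.7 gave 12% to 26%.

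**5. Missing visits.** Friedman needs all three time points. Without imputation, a patient who misses one visit drops out of it, although the analysis-set rule includes that patient.

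**The case against.** The primary model is right and matches the sample size; the defect sits in a conditional branch. Several points on the other side stand.

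- A reader might infer that efficacy goes wholly untested once the fallback is used. The text does not support that. Kruskal-Wallis of active versus sham at T1 or T2 is a valid randomised comparison with its type I error controlled. What is lost is the planned difference in change and, at higher correlations, power.
- The article does not say at which visit or on which quantity Kruskal-Wallis is run, nor that Friedman is run by arm. Kruskal-Wallis on change scores is not excluded, but it is not stated either.
- A reader might infer that normalisation can never succeed. The two techniques are introduced as examples, so others remain open. Percent change from baseline, or z-scores against age norms, would not be simple linear rescalings of the pooled data.
- Counting any disagreement between two by-arm Friedman tests gives 25% to 53%. That includes trials where only sham changed, so it is not a false-positive rate in favour of active.
- It is tempting to say the normality test will often fail. Under assumed shapes at n = 30, rejection ranged from about 9% (accuracy averaging 0.65, or some congruent-minus-incongruent scores) to over 80% (high accuracy). The article gives no trial counts, means or distributions, so the frequency is unknown.
- The missing-visit point is a tension, not a contradiction: it bites only if the fallback is used and visits are missed, and Kruskal-Wallis at a visit keeps everyone seen there.

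None of this puts a test of differential change into the fallback as written. Nor is it detail left to an analysis plan, since the article itself names the replacement tests.

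**Conclusion.** The concern holds in limited form and should be fixed. As written, the non-normal branch drops the treatment-by-time test on which the model, the sample size and the hypothesis depend, and the named normalising techniques, in their ordinary reading, cannot prevent this.

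If Kruskal-Wallis is run on raw T1 scores, power at the planned effect falls from 0.80 to about 0.74, 0.53 or 0.39 at ρ = 0.5, 0.7 or 0.8. If Friedman were run by arm, a spurious active-only result would appear in about 11% to 26% of trials over the settings run. These sizes rest on assumed correlations, normal data, an equal effect at T1 and T2, and common training gains of 0.3 to 0.7 SD. The structural point needs none of these assumptions.

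**What to change.** Keep treatment-by-time as the efficacy test in every branch:

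1. Check normality on the LMM residuals, not on the raw data.
2. Replace z-scores and percentage points with methods that change the shape or the model, for example a log transformation for reaction time, and a logit transformation or binomial mixed model for accuracy.
3. If residuals remain poor, replace Kruskal-Wallis and Friedman with a rank or permutation test of active versus sham on change from baseline, fixing in advance whether that is T1 − T0, T2 − T0 or their mean.

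The cost is analysis wording only; no new data are needed. One limit remains: a change-score test still omits patients without a baseline or the relevant follow-up visit, and the text should say so beside the intention-to-treat rule.
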